### Outcomes

The first aim of the study, characterising the natural history of severe early onset FGR, will involve multiple descriptive outcomes. The second aim, establishing a bio-bank, involves the creation of a resource for ongoing research with numerous potential endpoints. For the third aim, identifying prognostic markers, there will be two endpoints:

*Primary Endpoint*: Poor outcome, defined as fetal or neonatal death, including death in utero and within the first 28 days of life.

*Secondary Endpoint*: Time from enrolment to the end of pregnancy, defined as either diagnosis of stillbirth or delivery.

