**Methods:**

This is a 6 year European multicentre prospective cohort study, recruiting women with a singleton pregnancy where the EFW is <3rd centile for gestational age and <600 g at 20+0 to 26+6 weeks of gestation. Detailed data are collected on: maternal history; antenatal, peripartum, and postnatal maternal complications; health economic impact; psychological impact; neonatal condition, progress and complications; and infant growth and neurodevelopment to 2 years of corrected age in surviving infants. Standardised longitudinal ultrasound measurements are performed, including: fetal biometry; uterine artery, umbilical artery, middle cerebral artery, and ductus venosus Doppler velocimetry; and uterine artery and umbilical vein volume blood flow. Samples of maternal blood and urine, amniotic fluid (if amniocentesis performed), placenta, umbilical cord blood, and placental bed (if caesarean delivery performed) are collected for bio-banking. An initial analysis of maternal blood samples at enrolment is planned to identify biochemical markers that are predictors for fetal or neonatal death.

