#### Data collection

In order to fully characterise this cohort, an extensive data set is collected for each participant. This includes, but is not limited to, the majority of the optimal data set recommended by the Global Pregnancy CoLaboratory (COLAB) [28]. At enrolment maternal demographic, medical, obstetric, social, and family history are collected, as well as paternal demographic and family history and details of previously fathered pregnancies. Data are collected on the current pregnancy, including the results of ultrasound scans before and after enrolment, screening tests, invasive tests, and tests for maternal infection.

Data are collected about maternal antenatal, perinatal, and postnatal complications. Perinatal data are collected about the delivery, any maternal medication, the condition of the newborn and any need for resuscitation. For liveborn infants, data are collected at 4, 24 h, and 7 days of life as well as at discharge from the Neonatal Unit, if applicable. This includes data on cardiovascular, metabolic and respiratory status, growth, feeding, cranial ultrasound findings, retinopathy screening, and any medical or surgical complications. Surviving infants and children undergo neurodevelopmental follow-up until 2 years of age (corrected for prematurity, Table 1). Detailed health economic data are collected at approximately 6 weeks and 6 months post-delivery, including maternal and infant health service use and personal financial costs.

**Table 1 Tab1:** EVERREST Prospective Study infant neurodevelopmental follow-up plan

Age (corrected for prematurity)	3 months	6 months	12 months	24 months
Growth and health	X	X	X	X
Prechtl video assessment	X			
Amiel Tison neurological assessment, hearing, vision, and general assessment of development	X	X		
Hammersmith neuroassessment			X	X
Bayley III			X	X
Gross Motor Function Classification System (GMFCS)				X
Manual Ability Classification System (MACS)				X

All data are entered onto a central MACRO database using the participant’s unique Participation Identification Number. This password protected database is stored on servers based at University College London, which are protected by thorough electronic and physical security measures. Within the database electronic Case Report Forms include internal data checks for validity and consistency, and regular data checks are performed by the EVERREST Study Manager.

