### Sample analyses

Three initial analysis strategies are planned for maternal blood samples taken at study enrolment:Targeted angiogenic and anti-angiogenic markers: soluble FMS-like tyrosine kinase 1 (sFlt-1) and placental growth factor (PlGF) will be measured using the Roche Elecsys® automated electrochemiluminescence assay, VEGF-A, VEGF-D, soluble VEGF receptor-2, soluble endoglin, and neuropilin 1 will be measured using R&D Systems enzyme-linked immunosorbent assays (ELISAs).Semi-targeted vascular markers: 92 serum analytes implicated in cardiovascular disease will be measured on the Olink ProSEEK platform, using DNA primer-tagged antibody pairs in a proximity extension assay to provide very sensitive (1 uL serum) and specific measurements.Non-targeted proteomic analysis: a mass spectrometry-based serum profiling approach will be employed for the discovery of potential new biomarkers. Serum samples will be pooled into good and poor outcome groups and subjected to an established proteomic profiling workflow involving immunodepletion of the 12 most abundant serum proteins, tryptic digestion, 6-plex tandem mass tagging (TMT), and two-dimensional liquid chromatography (high and low pH reversed-phase) linked to quantitative tandem mass spectrometry. Candidate selection from the combined dataset will be based on standard statistical tests of fold-change, MS data quality and known function. Selected candidates will be further verified in the individual discovery samples using commercial ELISAs.

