### Statistical analysis

Characterising the natural history of severe early onset FGR (Aim 1) will involve descriptive statistical methods, including means for numerical variables and proportions for binary or categorical variables. An initial analysis is planned for the first 65 study participants to help refine the inclusion criteria for the EVERREST Clinical Trial.

The association between individual factors and outcome will be analysed using t tests and chi-squared tests, and non-parametric tests used if required (Mann–Whitney U tests and Fisher’s exact tests). Logistic regression modelling will be used to investigate whether individual and combinations of factors can be used to estimate poor outcome (primary endpoint). These factors include ultrasound findings, levels and ratios of angiogenic factors, and potential markers identified through the semi-targeted and proteomic approaches. Due to the relatively small sample size, a forward selection algorithm will be employed, and it is likely that each model will only sustain a maximum of two or three independent variables. Models will be tested for goodness of fit and discrimination using leave-one out cross validation and bootstrapping.

Survival analysis, including Cox proportional hazards regression, will be used to investigate the predictive value of individual and combined factors for the secondary outcome measure of time until the end of pregnancy.

An a priori sample size calculation is not provided, as there is currently no reliable data on expected means and standard deviations of candidate markers within such a cohort, and no data on whether and how these would differ by outcome. Within our current sample of 65, with 5 withdrawals and 18 poor outcomes, there is a ratio of good to poor outcomes of 2.33. This sample will give an 80% power to detect a standardised effect size of 1.0 to a significance level of 0.05 [36]. The potential for type 1 error, given the multiple comparisons, or type 2 error, given the small sample size, will be borne in mind when interpreting the study results.

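### The 28-day death window puts any later death in neonatal care into the good-outcome group for the prognostic-marker aim

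*Protocol article*

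**What the plan says.** The Outcomes section of the protocol article gives the third aim (prognostic markers) this primary endpoint: "Poor outcome, defined as fetal or neonatal death, including death in utero and within the first 28 days of life". The Abstract is consistent, speaking of "biochemical markers that are predictors for fetal or neonatal death".

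The good group is not defined separately. The Statistical analysis section reports "Within our current sample of 65, with 5 withdrawals and 18 poor outcomes" and says that "there is a ratio of good to poor outcomes of 2.33".

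The same section uses the split for the univariate tests and for the logistic models of the primary endpoint. Under Sample analyses it also underlies the untargeted proteomic step: "Serum samples will be pooled into good and poor outcome groups".

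The Data collection section gives this schedule for babies born alive: "data are collected at 4, 24 h, and 7 days of life as well as at discharge from the Neonatal Unit, if applicable". Survivors are then followed to 2 years of corrected age.

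**The concern.** Women enter at 20+0 to 26+6 weeks with an estimated fetal weight below 600 g, so some liveborn infants can be expected to be very preterm and to stay long in neonatal care. As an illustration, an infant born at 26+0 weeks reaches day 28 at 30+0 weeks postmenstrual age. A death in the unit after that is not a poor outcome under the definition, and no third category is described, so it falls into the comparison group.

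A marker that separates pregnancies ending in death from those with a surviving child would then be tested against a reference group containing some deaths. If those late deaths resemble the poor group on the marker, the observed difference shrinks.

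The proteomic pools are the least reversible use. Individual data can be recoded later, but a pooled sample cannot. Verification in individual samples reaches only the candidates that the pooled comparison has already selected.

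**Working it through.** **Inputs** (Statistical analysis section): 65 enrolled, 5 withdrawn, 18 poor; standardised effect d = 1.0; significance level 0.05, taken as two-sided because the article does not say. The number k of deaths after day 28 is not given, so it is an assumption, shown over a range.

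**The plan's own figures.**
- Ratio: (65 − 5 − 18)/18 = 42/18 = 2.33. This reproduces. All 60 non-withdrawn pregnancies are either poor or good, with nobody set aside.
- Power: the article states "This sample will give an 80% power to detect a standardised effect size of 1.0 to a significance level of 0.05". With 18 v 42, d/√(1/18 + 1/42) = 1.0/0.2817 = 3.55, which gives 94.4% by the normal approximation and 93.7% by the t test. The stated 80% does not reproduce; 80% corresponds to d of about 0.80. The stated figure is therefore conservative. That is separate from this point, and 93.7% is the baseline below.

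**Share of the good group.** For k = 1 to 4, k/42 runs from 2.4% to 9.5%. Counting those deaths as poor would raise the poor proportion from 18/60 = 30.0% to between 19/60 = 31.7% and 22/60 = 36.7%.

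**Dilution.** Assume that late deaths have the poor-group marker mean and that the within-group SD is 1. With p = k/42:
- difference in means = d(1 − p)
- variance of the good group = 1 + d²p(1 − p)
- pooled SD = √[(17 × 1 + 41 × variance of the good group)/58]
- observed d = difference in means / pooled SD

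For k = 4: p = 0.095; difference 0.905; variance 1.086; pooled SD 1.030; observed d = 0.88.

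| k (assumed) | k/42 | Observed d (true 1.0) | Power, left as good | Power, moved to poor |
|---|---|---|---|---|
| 0 | 0% | 1.00 | 93.7% | 93.7% |
| 1 | 2.4% | 0.97 | 92.2% | 94.3% (19 v 41) |
| 2 | 4.8% | 0.94 | 90.5% | 94.8% (20 v 40) |
| 4 | 9.5% | 0.88 | 86.6% | 95.6% (22 v 38) |
| 8 | 19.0% | 0.77 | 76.5% | 96.5% (26 v 34) |

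For a true effect of 0.8, power is 79.7% with no late deaths. With k = 4 it is 69.8% if they stay in the good group and 83.6% if they are moved.

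On the discrimination scale, under the same assumption with k = 3 and a true AUC of 0.75: 0.75 × 39/42 + 0.50 × 3/42 = 0.732.

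**The case against.** The strongest reply is that nothing here is wrong or contradictory. Twenty-eight days is the usual meaning of neonatal death, the Abstract and the Outcomes section agree, and keeping it preserves comparability. A sensitivity endpoint is also something a journal article may leave to the fuller protocol or analysis plan. This stands, and it is why the point is put as a design weakness with an addition as the remedy.

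The size is also uncertain. Eligibility fixes gestation at diagnosis, not at delivery, and the Discussion accepts that constitutionally small fetuses may be included. There may have been no late deaths. The ratio of 2.33 would be the same in that case, so it shows that nobody was set aside, not that any late death occurred. Late deaths may also arise from complications of prematurity and not share the enrolment marker profile, which would make the dilution smaller. Even on the assumptions used, 1 to 4 late deaths leave power at d = 1.0 above the stated 80%. All of this stands.

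The article does not list which samples enter the proteomic pools. That late deaths would be in the good pool is the natural reading, but it is an inference.

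A reader might infer three stronger things that the article does not support:
- **That the endpoint cannot be ascertained because no data point falls at day 28.** A date of death is enough.
- **That the planned Clinical Trial would count a delayed death as a success.** The Outcomes section ties this endpoint to the prognostic-marker aim only, and nothing says that it carries over.
- **That the primary endpoint should be replaced.** A discharge-based window differs in length between infants and depends on practice at four sites, so replacement is a trade-off and not a correction.

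**Conclusion.** The point holds in a limited form. By its definition, the primary endpoint for the prognostic-marker aim classes any death after day 28, including one in neonatal care, as a good outcome. This affects the tests, the logistic models and, on the natural reading, the proteomic pools.

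The size is unknown because the number of late deaths is not given. One to four among the 42, sharing the poor-outcome profile, would reduce an effect of 1.0 to about 0.97 to 0.88 and cost about 1.5 to 7 percentage points of power. The loss is greater for weaker markers: about 10 points at a true effect of 0.8 with four late deaths (79.7% to 69.8%). With no late deaths, or late deaths unrelated to the enrolment markers, there is little or no dilution. The case for acting rests mainly on how little the remedy costs and on the fact that pooled samples cannot be regrouped afterwards.

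**What to change.** Keep death in utero or within 28 days as the primary endpoint, and add:

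1. A pre-stated sensitivity endpoint for the third aim: death in utero or death before discharge from the Neonatal Unit, with the main tests and models repeated on it.
2. A report of the number of deaths after day 28, so that readers can judge how far the two endpoints differ.
3. A rule that pregnancies with such a death do not contribute serum to the good-outcome proteomic pool.

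No new data are needed, because status at Neonatal Unit discharge is already recorded. The costs are a little more analysis, possibly a few fewer samples in the good pool, and the need to know discharge status before pooling. The sensitivity window will also vary with gestation at birth and with site discharge practice, which should be said when it is reported.

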### Statistical analysis

Characterising the natural history of severe early onset FGR (Aim 1) will involve descriptive statistical methods, including means for numerical variables and proportions for binary or categorical variables. An initial analysis is planned for the first 65 study participants to help refine the inclusion criteria for the EVERREST Clinical Trial.

The association between individual factors and outcome will be analysed using t tests and chi-squared tests, and non-parametric tests used if required (Mann–Whitney U tests and Fisher’s exact tests). Logistic regression modelling will be used to investigate whether individual and combinations of factors can be used to estimate poor outcome (primary endpoint). These factors include ultrasound findings, levels and ratios of angiogenic factors, and potential markers identified through the semi-targeted and proteomic approaches. Due to the relatively small sample size, a forward selection algorithm will be employed, and it is likely that each model will only sustain a maximum of two or three independent variables. Models will be tested for goodness of fit and discrimination using leave-one out cross validation and bootstrapping.

Survival analysis, including Cox proportional hazards regression, will be used to investigate the predictive value of individual and combined factors for the secondary outcome measure of time until the end of pregnancy.

An a priori sample size calculation is not provided, as there is currently no reliable data on expected means and standard deviations of candidate markers within such a cohort, and no data on whether and how these would differ by outcome. Within our current sample of 65, with 5 withdrawals and 18 poor outcomes, there is a ratio of good to poor outcomes of 2.33. This sample will give an 80% power to detect a standardised effect size of 1.0 to a significance level of 0.05 [36]. The potential for type 1 error, given the multiple comparisons, or type 2 error, given the small sample size, will be borne in mind when interpreting the study results.

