The EVERREST Prospective Study has been designed to support the development and conduct of the EVERREST Clinical Trial, but we believe that its findings will have wider applications. By providing outcome data and prognostic markers for a severe early onset subset of FGR, this study is likely to improve future patient counselling and guide clinician’s management. The bio-bank of comprehensively phenotyped samples will also support future research into the biological mechanisms underlying FGR, and hopefully identify novel targets for future therapies.

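### A limit of two or three retained variables does not protect the prognostic model against forward selection among about 100 candidates, so ordinary logistic coefficients are likely to be too extreme

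*Protocol article*

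**What the plan says.** All of this is in the protocol article, Methods.

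- Purpose (Statistical analysis): "Logistic regression modelling will be used to investigate whether individual and combinations of factors can be used to estimate poor outcome".
- Response to small numbers (same section): "Due to the relatively small sample size, a forward selection algorithm will be employed".
- Expected model size (same section, given directly after that choice): "it is likely that each model will only sustain a maximum of two or three independent variables".
- Numbers so far (same section): "Within our current sample of 65, with 5 withdrawals and 18 poor outcomes, there is a ratio of good to poor outcomes of 2.33".
- Candidates: Sample analyses lists seven angiogenic or anti-angiogenic markers and a 92-analyte vascular panel, followed by an untargeted proteomic search. Statistical analysis adds ultrasound findings and ratios.
- Checks (Statistical analysis): goodness of fit and discrimination are to be tested by leave-one-out cross-validation and bootstrapping. Type 1 and type 2 error are to be kept in mind in interpretation.

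Nothing is said for or against shrinking or penalising the coefficients.

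**The concern.** Small numbers are given as the reason for forward selection, but they are a reason for caution about it. Each step picks the candidate that looks strongest in these women, and with few events part of that strength is chance. The chance part grows with the number of candidates searched, whatever the number kept. A three-variable model drawn from 99 candidates is therefore far more overfitted than one whose three variables were named beforehand, yet the stated limit treats the two alike.

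The effect falls on the size of the coefficients. If they are inflated, predicted risks are pushed towards 0 and 1. Discrimination does not show this directly, because a model can rank women usefully and still give wrong risks. Poor fit in resampling can show it, but observing a problem does not alter the coefficients. If risks or a risk threshold were later read off the model, the women labelled highest risk would have a true risk well below the stated one.

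**Working it through.** **Inputs from the article.** 65 − 5 − 18 = 42 good outcomes, and 42/18 = 2.33, so the stated ratio reproduces. The analysable sample is 60, with an event rate of 18/60 = 0.30. Events per retained variable are 18/2 = 9 or 18/3 = 6. Candidates: 7 + 92 = 99 as a minimum. The article's power statement concerns one comparison of means and has no bearing on the model.

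**Step 1: variables named in advance.** The expected calibration slope S of an unpenalised model with P parameters solves n = P / [(S − 1) ln(1 − R²/S)]. Here R² is the Cox-Snell value, whose maximum at 30% events is 1 − exp[2(0.3 ln 0.3 + 0.7 ln 0.7)] = 0.705. The article gives no explained variation, so I assume Nagelkerke R² of 0.15, 0.30 and 0.50.

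| Nagelkerke R² | S, P = 2, n = 60 | S, P = 3, n = 60 | Women per parameter for S = 0.9 |
|---|---|---|---|
| 0.15 | 0.77 | 0.70 | 80 |
| 0.30 | 0.88 | 0.83 | 37 |
| 0.50 | 0.93 | 0.90 | 20 |

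Example for the last column: R² = 0.30 × 0.705 = 0.212, and 1/[−0.1 × ln(1 − 0.212/0.9)] = 37. At S = 0.9, 60 women support 60/80 = 0.75 to 60/20 = 3 parameters. Two or three variables is thus a defensible limit only when the markers are strong and prespecified.

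**Step 2: variables found by search.** Simulation: development sets of 18 v 42; independent normal markers, three of them truly prognostic with the mean shift shown; forward selection at p < 0.05 with at most three kept; performance measured in new women. Effects, independence and the entry rule are my assumptions. Entries are calibration slopes; ranges are the spread over repeated runs.

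| True shift of each marker | Three prespecified | Selected from 20 | Selected from 99 |
|---|---|---|---|
| 0.45 SD | 0.69–0.70 | 0.26–0.27 | 0.02–0.09 |
| 0.7 SD | 0.77–0.80 | 0.48 | 0.20–0.22 |
| 1.0 SD | 0.81–0.83 | 0.54–0.57 | 0.37–0.42 |

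Other mixtures of effects gave 0.62–0.78 prespecified, 0.26–0.49 from 20 and 0.10–0.28 from 99.

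**Step 3: what this does to risks.** Mean predicted v true risk in the tenth of women ranked highest:

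| True shift | Three prespecified | Selected from 20 | Selected from 99 |
|---|---|---|---|
| 0.45 SD | 0.67 v 0.57 | 0.75 v 0.43–0.45 | 0.87–0.88 v 0.36–0.37 |
| 1.0 SD | 0.93 v 0.90 | 0.93–0.94 v 0.82 | 0.95–0.96 v 0.72–0.75 |

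The search, and not three variables on 18 events, produces the large errors.

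**Step 4: does shrinkage help?** A uniform bootstrap factor was applied after selection from 99, with selection repeated in each resample and the intercept re-estimated. The top-tenth prediction fell from 0.88 to 0.55–0.56 (true 0.35–0.37) at 0.45 SD, and from 0.90–0.91 to 0.61–0.62 (true 0.50–0.52) at 0.7 SD. At 1.0 SD it fell from 0.96 to 0.73 (true 0.75). The gain is large, but correction is incomplete unless the markers are strong.

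**The case against.** The strongest reply is that this is a condensed article. It says logistic regression and no more on estimation, so unpenalised coefficients are an inference from silence; a full protocol or analysis plan may well specify shrinkage. That stands, and the absence of shrinkage is not itself the fault. What the article does state is the remedy for small numbers, forward selection with a limit on retained variables, and that remedy does not address the search.

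Second, goodness of fit is to be tested alongside discrimination, with resampling. This could expose miscalibration, and the bootstrap is the very tool needed to correct it. That also stands: the machinery is planned, but its stated use is testing only.

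Third, the semi-targeted and proteomic work may hand the model a shortlist, not 99 markers. But the article points to no separate women for that shortlisting, and its proteomic candidates are verified in the same discovery samples. A shortlist chosen on the same outcomes carries the search with it. Even a true pool of 20 gives slopes of about 0.3 to 0.6.

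Fourth, a reader might infer that women will be told risks near certainty, or that trial eligibility will rest on a model cut-off. The article does not say so. Modelling is to investigate whether factors can be used; markers may help refine later eligibility; and "this study is likely to improve future patient counselling" refers to the study as a whole. The planned look at the first 65 participants to refine trial inclusion criteria sits with the descriptive analyses and is not tied to this model.

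**Conclusion.** The concern holds in this form: forward selection from a pool of this size, with a cap only on variables kept, is likely to give coefficients that are too extreme, and the planned tests do not correct them. Expected slopes are about 0.7 to 0.8 for three prespecified variables, 0.3 to 0.6 from 20 candidates and 0 to 0.4 from 99.

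These figures rest on assumed marker effects, independent markers, an assumed entry rule, ordinary maximum likelihood, and 18 v 42. The last is the current count in a six-year study and not a stated final number; more events would lessen the problem. Correlated markers would change the effective number of candidates.

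A tempting stronger reading is that three variables on 18 events alone make the risks far too extreme. The figures do not support it: with prespecified variables the overfitting is moderate. Nor does the article commit to unshrunken coefficients. It is a worthwhile, inexpensive improvement to a stated method.

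**What to change.** Keep logistic regression and the discovery work, and add to the Statistical analysis section or the analysis plan:

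1. Estimate a uniform shrinkage factor from the bootstrap already planned, repeating the whole selection, including any univariable screening, in every resample. Alternatively, fit a penalised model such as ridge or lasso over the candidates.
2. Multiply the coefficients by the factor and re-estimate the intercept so that mean predicted risk matches the observed rate.
3. Report the optimism-corrected calibration slope with each model.
4. Derive no absolute risk or risk cut-off from unshrunken coefficients.
5. State that the limit of two or three variables does not protect against selection among about 100 candidates. A cap on candidates is not the answer, since it would end the planned marker search.
6. Call any resulting model exploratory until it is validated in other women, because shrinkage reduces the over-extremity without reliably removing it.

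Cost: some wording, standard software and a little more analysis work. Published odds ratios and risks will be less striking and slightly biased towards the mean. No new data collection is needed for items 1 to 5.

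### If cross-validation and bootstrapping are applied to models already selected by outcome from at least 99 candidates, the reported discrimination is inflated, and the proteomic step as described cannot be nested

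*Protocol article*

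**What the plan says.** The steps are spread over two sections of the protocol article.

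- **Candidates (Sample analyses).** Seven targeted angiogenic markers are measured: sFlt-1, PlGF and five others by ELISA. In addition, "92 serum analytes implicated in cardiovascular disease will be measured on the Olink ProSEEK platform". A mass spectrometry arm compares serum pooled by good and poor outcome, and its candidates are then verified by ELISA in the individual samples that made up the discovery set.
- **What enters the models (Statistical analysis).** "These factors include ultrasound findings, levels and ratios of angiogenic factors, and potential markers identified through the semi-targeted and proteomic approaches".
- **Selection (same section).** Because the sample is small, "a forward selection algorithm will be employed, and it is likely that each model will only sustain a maximum of two or three" independent variables.
- **Validation (same section).** "Models will be tested for goodness of fit and discrimination using leave-one out cross validation and bootstrapping".
- **Sample (same section).** "Within our current sample of 65, with 5 withdrawals and 18 poor outcomes, there is a ratio of good to poor outcomes of 2.33".

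For multiplicity, the section promises only caution in interpretation. No set of women outside the discovery samples is named for testing the models.

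**The concern.** The one stated restraint on overfitting is the cap of two or three variables. That limits the final model, but the optimism comes mainly from the size of the pool searched. A variable picked because it separated these 18 poor outcomes from the rest will keep separating them when its coefficient is refitted with one woman left out. Resampling a model after its variables have been chosen on all the outcomes therefore corrects for estimating coefficients but not for choosing variables.

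Prognostic markers are the third aim, and fetal or neonatal death is its primary endpoint. The Discussion expects markers possibly to refine eligibility for later-phase trials, and the study's outcome data and markers to improve counselling and guide management. A cross-validated figure that still carries selection optimism would look to those users like evidence that a model had been validated.

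**Working it through.** **1. Sample.** 65 − 5 = 60 women; 60 − 18 = 42 good outcomes; 42/18 = 2.33. The stated ratio reproduces. The power sentence beside it does not. With 18 against 42 and a standardised effect of 1.0, two-sided 0.05 (sidedness assumed), power = Φ(1.0/√(1/18 + 1/42) − 1.96) = Φ(3.55 − 1.96) = Φ(1.59) = 94.4%, not 80%. That figure concerns a single-marker comparison, errs on the cautious side, and has no bearing on this point.

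**2. Pool searched.** 2 + 5 + 92 = 99 named markers. This is a lower bound, since ratios, ultrasound findings and proteomic candidates come on top.

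- Events per variable in the final model: 18/2 = 9 or 18/3 = 6.
- Events per candidate searched: 18/99 = 0.18.
- If no marker is prognostic and tests are independent at 0.05: 99 × 0.05 = 4.95 false positives expected, and P(at least one) = 1 − 0.95^99 = 99.4%.

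**3. Null simulation.** 60 women, 18 events, normal markers unrelated to outcome, forward logistic selection by score test. The entry threshold is an assumption, because the article gives none. There were 300 runs per setting (200 where a t-test screen at p<0.05 on all the data came first). The table shows mean AUC; a useless model has a true AUC of 0.50. There are 99 candidates unless stated.

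| Repeated in each resample | Setting | Apparent | Leave-one-out | Bootstrap-corrected |
|---|---|---|---|---|
| Nothing (selected model only) | max 2, p<0.05 | 0.79 | 0.74 | 0.77 |
| Nothing | max 3, p<0.05 | 0.84 | 0.78 | 0.81 |
| Nothing | max 2, markers correlated 0.5 in blocks of 10 | 0.77 | 0.72 | 0.75 |
| Nothing | max 3, same correlation | 0.81 | 0.76 | 0.78 |
| Nothing | max 1, p<0.05 | 0.71 | 0.67 | 0.71 |
| Nothing | max 3, p<0.01 | 0.67 | 0.65 | 0.67 |
| Nothing | 7 candidates, max 2, p<0.05 | 0.56 | 0.55 | 0.56 |
| Forward step only, after full-data screen | max 2, p<0.05 | 0.78 | 0.56 | 0.71 |
| Forward step only, after full-data screen | max 3, p<0.05 | 0.81 | 0.61 | 0.74 |
| All selection | max 2, p<0.05 | 0.79 | 0.47 | 0.62 |
| All selection | max 3, p<0.05 | 0.84 | 0.47 | 0.65 |

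With the selected model only, leave-one-out AUC reached 0.70 or more in 82% of runs (two variables) and 96% (three). With all selection repeated it did so in about 10%. A separate simulation with the same pool and event split gave 0.73 and 0.78 for the selected model, and 0.46 to 0.50 with selection nested.

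**4. Proteomic step.** Candidates come from comparing outcome-defined pools and are verified in the samples that formed those pools. Each contributing woman's outcome has already shaped the list, and pooled measurements cannot be split again to leave her out. Nesting is therefore not available for this step as described, whatever the software does later.

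**The case against.** The strongest reply is that the article never says selection stays outside the resampling. It is a condensed account, a full analysis plan may exist, and leave-one-out with all selection repeated removes the bias. This stands as a limit on the claim. A reader might infer that the study will report good discrimination even if nothing is prognostic, so that its validation merely endorses noise. The documents do not support that: the inflation is conditional on how the resampling is run.

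Other points against the larger figures:

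- **Entry threshold.** It is unstated, and p<0.01 lowers the null leave-one-out AUC to 0.65. This stands, so a range is needed rather than one number.
- **Prior narrowing.** The text suggests that panel markers are identified before modelling. If the forward step is then repeated, leave-one-out falls to 0.56 to 0.61. This stands in part, because the bootstrap still gives 0.71 to 0.74.
- **Event count.** Eighteen is the current count in a six-year cohort, and nothing confines the third aim to the first 65 women. This stands, since more events would shrink the inflation.
- **Importance of the AUC.** The article speaks of discrimination and lists ROC only among its abbreviations. It does not call an AUC the main result of the third aim. This stands.
- **Acknowledged type 1 error.** The article recognises multiple comparisons, but caution in interpretation does not correct a reported measure of discrimination.

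An unseen analysis plan could settle how the panel and targeted markers are handled. It could not make the pooled proteomic step repeatable by fold. That part rests on what the article states, not on what it omits.

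**Conclusion.** The concern holds conditionally. On the natural reading, where validation is applied to the selected models, and with no prognostic marker in the current 60 women, leave-one-out AUC averages about 0.73 to 0.78 for two or three variables at entry p<0.05, and about 0.65 at p<0.01. Repeating only the forward step leaves 0.56 to 0.61 (bootstrap 0.71 to 0.74). Full nesting brings leave-one-out to about 0.46 to 0.50.

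These sizes assume 99 candidates, 18 events and an entry rule that the article does not give. They were obtained with independent markers; correlation lowers the selected-model figures slightly, to 0.72 to 0.76.

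The proteomic part does not depend on the reading. Candidates found and verified in the same outcome-sorted samples cannot be validated in those samples.

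**What to change.** In the Statistical analysis section, state that every step that uses outcome (univariable screening, marker identification, forward selection and fitting) is repeated within each cross-validation fold. The nested cross-validated discrimination should be the primary performance measure. A bootstrap optimism correction may be shown beside it but is not sufficient alone: even with selection repeated it gave 0.62 (two variables) and 0.65 (three) when no marker was prognostic.

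Report proteomic candidates found in these women as discovery only. Leave them out of any model described as validated until a locked model has been tested in participants outside the discovery set.

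Penalised regression in place of forward selection is optional, since nested forward selection already removes the upward bias in leave-one-out.

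The cost is revised analysis wording, a little more computing and a less favourable reported AUC. Testing proteomic candidates must also wait for women outside the discovery set.
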